### Sample size calculation

The sample size was determined using SMI changes. A previous study demonstrated that the 28-week intervention with HI-RT and protein supplementation changed the SMI, with values of -0.03 ± 0.21 in the control group and 0.30 ± 0.22 in the intervention group [14]. A two-tailed, T-test-based sample test was performed according to the previous trial; the calculated sample size of 13 participants per group corresponds with a 95% power (1-β), type-I alpha error =0.05, and effect size of d=1.53. We decided to include at least 17 people each group, assuming a 25% dropout rate.

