### Statistical analysis

All analyses will be carried out using IBM SPSS Statistics (version 23.0; IBM, Armonk, New York, USA), with a significance level of 5% and a 95% CI. Descriptive statistics will be applied to present the subject demographics. Intention-to-treat analysis will be performed to analyze the results, and the independent T-test will be used to compare the baseline values between groups. For the analysis of primary outcomes, independent t-test or Mann-Whitney U test for comparisons between changes from the baseline to the end of the intervention will be applied according to the distribution of data by Shapiro-Wilk test. The data will be described using means, standard deviations, and 95% confidence intervals (CIs). The method for handling missing data will be chosen after the study is finished based on the distribution of the data. A mixed-effects model or generalized estimating equations will be employed using one between-subject factor (group: intervention and control) and one within-subject factor to compare the secondary outcomes and find differences in outcomes between groups with time.

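### Primary outcomes are compared as raw changes, with the test chosen by a normality pretest: the effect measure is left to the data and chance baseline imbalance is not adjusted for

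*Protocol article*

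**What the plan says.** The Statistical analysis section of the protocol article fixes the primary analysis as follows: "independent t-test or Mann-Whitney U test for comparisons between changes from the baseline to the end of the intervention will be applied", and the choice between the two is made "according to the distribution of data by Shapiro-Wilk test". It states neither the level of that normality test nor whether it is run per arm or pooled. No covariate is named for the primary outcomes.

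The same section adds that "the independent T-test will be used to compare the baseline values between groups", and on presentation: "The data will be described using means, standard deviations, and 95% confidence intervals (CIs". A mixed model or GEE is named for the secondary outcomes only.

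Under Primary outcome measurement, the primaries are the 24-week changes in SMI, lumbar spine BMD and total hip BMD by DXA. The T0 value of each is therefore needed in any case. The Sample size calculation rests on a comparison of means: "A two-tailed, T-test-based sample test was performed according to the previous trial", using SMI changes with "values of -0.03 ± 0.21 in the control group and 0.30 ± 0.22 in the intervention group".

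**The concern.** Two features of the stated method cause difficulty.

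- **The effect measure is not fixed.** A t-test addresses a difference in means; Mann-Whitney addresses a rank ordering. With a pretest deciding outcome by outcome, SMI could be judged on means and hip BMD on ranks. Where Mann-Whitney is selected, the p-value no longer belongs to the mean difference on which the trial was sized, and means with SDs and CIs do not summarise the comparison that was tested.
- **Chance baseline imbalance stays in the estimate.** In an imperfectly repeatable measure, the arm that happens to start higher tends to show the smaller change. A raw change score carries that regression to the mean into the treatment comparison. A significance test on baseline values in a randomised trial only describes chance; it adjusts nothing.

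At stake are the clarity of the primary result and its robustness to the luck of a 34-person allocation, more than its power.

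**Working it through.** **1. The plan's own figure.** From the SMI changes in the Sample size calculation: difference = 0.30 − (−0.03) = 0.33; pooled SD = √((0.21² + 0.22²)/2) = 0.215; d = 0.33/0.215 = 1.53. The two-sided t-test at α = 0.05 and 95% power (noncentral t) needs 12.1, so 13 per group, as stated. Power at 13 is 96.3%. The stated size reproduces, and it is the size for a mean comparison.

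**2. The pretest.** Simulation, 10,000 trials per setting, 13 and 17 per arm. Assumption, because the plan is silent: Shapiro-Wilk at 0.05 in each arm, Mann-Whitney if either arm rejects. Settings: normal, t with 3 df, lognormal and exponential changes.

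| Quantity | Normal changes | Skewed or heavy-tailed changes |
|---|---|---|
| Share of trials sent to Mann-Whitney | 9–10% | 41–94% |
| t-test and Mann-Whitney disagree on significance at d = 0.72 | 7–8% | 12–22% |
| Type I error of the two-stage rule | 5.2–5.4% | 4.9–5.6% |

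The value 0.72 is the BMD standardised difference that the Background quotes from the earlier trial in men at 18 months. It serves here only as an example of a moderate effect.

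**3. Size of chance imbalance.** In baseline-SD units the between-arm difference has standard deviation √(2/n): 0.343 at n = 17 and 0.392 at n = 13. Hence P(|imbalance| > 0.5 SD) = 0.145 and 0.202 for a given outcome.

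**4. What that does to a raw change score.** Let r be the correlation between baseline and week 24 (not in the documents; assumed), with equal variances. A baseline difference of 0.5 SD shifts the expected change difference by 0.5(1 − r) baseline SD. The SD of change is √(2(1 − r)) baseline SD. The shift in change-SD units is therefore 0.5·√((1 − r)/2):

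| r | Conditional bias (change-SD) | Share of d = 1.53 | Share of d = 0.72 |
|---|---|---|---|
| 0.80 | 0.16 | 10% | 22% |
| 0.90 | 0.11 | 7% | 16% |
| 0.95 | 0.08 | 5% | 11% |

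For SMI, with a change SD of 0.215, that is 0.017 to 0.034 kg/m² against a planned 0.33. The standard error of the comparison at 17 per arm is √(2/17) = 0.343 change-SD, so the bias is about a quarter to a half of one standard error.

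**5. Precision of the adjusted analysis.** Variance relative to the change score = (1 + r)/2 × (1 + 1/(2n − 4)); the second factor is the cost of estimating the slope.

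| r | Ratio, 17 per arm | Ratio, 13 per arm | SMI power, 13 per arm |
|---|---|---|---|
| 0.80 | 0.93 | 0.94 | 97.1% |
| 0.90 | 0.98 | 0.99 | 96.4% |
| 0.95 | 1.01 | 1.02 | 96.0% |
| 0.98 | 1.02 | 1.04 | 95.7% |

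The ratio reaches 1 at r = 60/31 − 1 = 0.935 (17 per arm) and r = 44/23 − 1 = 0.913 (13 per arm). For SMI, r = 1 − 0.215²/(2S²) for an assumed baseline SD S: 0.74 at S = 0.3, 0.86 at 0.4, 0.91 at 0.5 and 0.94 at 0.6 kg/m².

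**The case against.** The best defence is that little is lost inferentially. Under randomisation the change-score comparison is unbiased over all allocations. The two-stage rule holds its type I error, its power is not harmed, and SMI already has about 96% power at 13 per arm. All of that stands.

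Several stronger readings are tempting and should not be drawn:

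- **That baseline adjustment is simply more precise, or would save participants.** The familiar ratio (1 + r)/2 omits the cost of estimating the slope. The documents give no r, and a 24-week DXA measure could lie above break-even (an assumption either way).
- **That the pretest inflates type I error or loses power.** Step 2 shows no material inflation. The power of Mann-Whitney on normal data is not the power of this plan, which would use that test there in only about 9–10% of trials.
- **That a stated share of trials would switch at least one primary.** This needs the dependence among the three outcomes, as well as the level and form of the pretest. None of these is given.
- **That the plan promises a CI for the between-group mean difference, or relies on the baseline t-tests to deal with imbalance.** The text says only that data will be described with means, SDs and CIs, and that baselines will be compared. It gives no purpose for the latter.

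It could also be said that an analysis plan not shown may settle these points. But the article names the test, the switch and the outcome scale, so this is a matter of stated method and not of omitted detail.

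**Conclusion.** The point holds in a limited form. The primary effect measure is chosen by the trial's own data, can differ across the three primaries, and may not match the t-test-based sample size or the planned summaries. The measured baseline is left unused as a covariate in a trial small enough for imbalance to matter in roughly one in seven to one in five allocations per outcome. The conditional bias at a 0.5 SD imbalance is about 0.08 to 0.16 change-SD: small against the planned SMI effect, less so against a BMD effect near 0.72. These sizes rest on an assumed r of 0.95 to 0.8 and equal variances; the pretest frequencies rest on per-arm testing at 0.05.

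A reader might infer that adjustment settles the estimand. It settles only the summary measure. Missing-data handling, which the same section defers until after the study, is untouched. The change is worth making because it is nearly free, not because the current test is invalid.

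**What to change.** For each primary outcome, prespecify one model: the week-24 value regressed on group and the baseline value of that outcome (or an equivalent baseline-adjusted mixed model). Report the adjusted mean difference with its 95% CI. Delete the Shapiro-Wilk switch and the baseline significance tests, keeping baseline values as descriptive summaries. Retain a rank-based, bootstrap or permutation analysis as a sensitivity analysis only, whatever the residuals look like.

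The cost is a change of wording and one degree of freedom; no new data are needed. If r is very high, the variance rises by about 1% to 2% at 17 per arm (2% to 4% at 13). The sample size need not change: the adjusted analysis still needs no more than 13 per arm for 95% power on SMI at every r examined (0.5 to 0.98). Any statement of benefit should call the precision gain modest and dependent on the correlation.

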### Primary outcome measurement

The primary outcomes of this trial will be changes in the SMI and BMD of the lumbar spine and total hip using DXA (Hologic, Marlborough, Massachusetts, USA) analysis from the baseline to end of intervention (24 weeks). Changes in body composition will be repeatedly measured at T0 (0 weeks), T2 (12 weeks), and T4 (24 weeks) to evaluate the effects of resistance training and nutritional support, as well as whether the effect gain by the intervention is maintained after training (Fig. 4).

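### The missing-data method is to be chosen from the data after the study ends, so the intention-to-treat primary analysis is undefined for the quarter of women expected to drop out

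*Protocol article*

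**What the plan says.** In the protocol article, the Statistical analysis section promises an intention-to-treat analysis. It tests the primary outcomes by comparing changes from baseline to the end of the intervention between the two arms, with a t-test or a Mann-Whitney test depending on a normality check. On incomplete data it says: "The method for handling missing data will be chosen after the study is finished based on the distribution of the data". For the secondary outcomes only, "A mixed-effects model or generalized estimating equations will be employed".

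The Sample size calculation section bases the trial on a two-sided t-test with "type-I alpha error =0.05" and planning changes in SMI with "values of -0.03 ± 0.21 in the control group and 0.30 ± 0.22 in the intervention group". It arrives at 13 per group and adds: "We decided to include at least 17 people each group, assuming a 25% dropout rate". The Exit criteria list non-completion of the protocol as a reason for leaving the study. The Primary outcome measurement section schedules body composition at 0, 12 and 24 weeks. It does not expressly say that lumbar spine and hip bone density are also scanned at 12 weeks, and the schedule figure is not shown.

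**The concern.** A change score needs a 24-week value. A woman without one is either left out or given a value by whatever method is picked later. That later choice therefore settles who is in the primary analysis and with what data, which is what an intention-to-treat plan should settle beforehand.

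The criterion for choosing does not help. The distribution of the observed values cannot show why other values are missing, so it cannot justify one method over another. The article gives no default and no decision rule, and does not say that whoever chooses will be masked to group. Dropout could also differ between arms, because only the exercise arm attends the gym twice a week.

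At stake is the credibility of the primary estimate. With about a quarter of values missing, both its size and, less often, its significance can depend on a decision taken once the data are known.

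**Working it through.** **Inputs from the Sample size calculation section.** Change in SMI: control −0.03 (SD 0.21), intervention 0.30 (SD 0.22). Two-sided alpha 0.05, 95% power, 13 per group raised to 17 for 25% dropout.

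**Assumptions, not in the document.** Changes are normally distributed. Four of 17 are missing per arm, at random unless stated. The mean change at 12 weeks is half that at 24 weeks, its SD is 0.8 of the 24-week SD, and the two changes correlate 0.6. Every dropout has a 12-week value. There were 20,000 simulated trials per scenario.

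**1. The plan's own figure.** Pooled SD = √((0.21² + 0.22²)/2) = √0.04625 = 0.215, and d = 0.33/0.215 = 1.53, as stated. From the noncentral t distribution, power is 94.7% with 12 per group and 96.2% with 13, so 13 is reproduced. 13 × 1.25 = 16.25 gives 17. (Dividing, 13/0.75 = 17.3, would give 18; with 12 and 13 evaluable women power is still 95.5%, so power is not the issue.)

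**2. How much is missing.** 17 × 0.25 = 4.25, so about 4 per arm, leaving 13.

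**3. The estimate under different methods at the planning difference.**

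| Handling of the 4 missing women per arm | Calculation | Estimated difference |
|---|---|---|
| Complete cases | 0.33 | 0.33 |
| 12-week value carried forward | (13/17) × 0.33 + (4/17) × 0.165 | 0.29 |
| Baseline carried forward | (13/17) × 0.33 + 0 | 0.25 |
| Control mean change for all missing | (13/17) × 0.33 + 0 | 0.25 |

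The simulated averages agree: 0.330, 0.291, 0.252 and 0.252.

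**4. Type I error with no true effect.** Complete cases, baseline carried forward and 12-week value carried forward reject in 5.0%, 4.9% and 4.9% of trials. Taking the smallest of the three p-values rejects in 6.9%; repeat simulations gave 7.0% to 7.4%.

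**5. How often the choice decides significance.** At a difference of 0.33 the three methods have 96.3%, 95.4% and 97.8% power and disagree in 3.4% of trials. At an assumed difference of 0.18, power is 53.5%, 52.3% and 58.2%, and they disagree in 15.7%.

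**6. Informative dropout (assumed).** Suppose there is no true effect but poorer responders in the exercise arm are likelier to leave. Complete-case analysis is then biased by +0.047 and rejects in 9.6% of trials; the most favourable of the three methods rejects in 11.4%. Most of this excess comes from the dropout itself, and the later choice adds the rest.

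**The case against.** The strongest reply is that the damage is limited. At the planning difference every ordinary method has at least 95% power, and they rarely disagree. The 7% is a ceiling: it supposes that someone picks the smallest p-value, whereas the article ties the choice to the data's distribution and not to significance. The 15.7% disagreement needs a smaller effect that the document does not state. All of this stands and limits the size of the point. It does not remove it, because the rule still leaves the estimate open until the data are known, and an unseen analysis plan could cure that only by contradicting the published sentence.

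Four stronger readings are tempting, and the document does not support them.

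- *The analysis is not intention-to-treat.* It is promised; what is lacking is a definition.
- *Type I error could reach about 14%.* That arises only if single mean imputation is among the candidates. That method rejects at about 14% on its own, so fixing it in advance would be just as bad. The article does not mention it, and the figure does not measure the cost of choosing late.
- *Week-12 data from dropouts are thrown away.* Nothing says so. The method is open, and some candidates would use them.
- *Generalized estimating equations endanger the primary result.* They are listed for the secondary outcomes only.

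**Conclusion.** The point holds: the article commits to choosing the missing-data method after the fact, on a criterion that cannot identify a valid method, for a primary test that cannot handle a missing 24-week value. The SMI estimate could move between about 0.25 and 0.33 at the planning difference, significance would change in about 3% of trials there, and type I error would rise to at most about 7% under missingness at random.

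These sizes depend on the assumed 4 missing per arm, the assumed link between 12- and 24-week changes, and the three methods compared. The range of estimates follows from simple arithmetic and is the firmest part. Sample size and planned power are not affected. Naming a method in advance removes the choice; it does not by itself remove bias from informative dropout, which is why a sensitivity analysis is also needed.

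**What to change.** By dated amendment before unblinding, replace the sentence with one prespecified method.

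- **Primary method, for example:** a REML mixed model for repeated measures on all randomised women as assigned, with baseline as covariate and the week-24 group contrast as primary. Use week-12 values where they are measured: SMI, and bone density only if it is scanned then. State that a woman with no value after baseline adds no outcome information to this model. If bone density is not scanned at week 12, its model reduces to a baseline-adjusted comparison at week 24. Prespecified multiple imputation would also meet the point.
- **One sensitivity analysis:** give exercise-arm dropouts the control-arm mean change. Assuming no change instead would be kinder to the exercise arm, because the planning control mean is −0.03. With 4 of 17 missing, the planning estimate would be (13/17) × 0.30 + 0.03 = 0.259 under no change, against (13/17) × 0.30 + (4/17) × (−0.03) + 0.03 = 0.252 under the control mean.

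The cost is statistical wording only. The article already lists a mixed-effects model for the secondary outcomes, and no new data or participants are needed. The drawback of the mixed model is that the primary test then differs from the t-test used for sizing, although the sample size stands. If group-labelled data have already been seen, report the method as chosen afterwards and show the primary result under each reasonable alternative.

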### Predicted adverse events and monitoring

The potential for adverse events and risks, as reviewed by the institutional review board and primary investigator, will be minimal. The potential adverse events that could occur in the exercise group during the intervention will be observed by therapists include fatigue, arthralgia, exercise-induced injuries, or falls; participants in the control group will not be queried regarding adverse events. Additionally, the therapists will report the primary research coordinator and handle the problem as quickly as feasible if the patient's discomfort during exercise worsens or if the symptoms will not go away before the next exercise session. The number and seriousness of the adverse events will be reported.

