#### Exit criteria

The exit criteria will be as follows: 1) participants’ request, 2) serious side effects preventing further participation, and 3) not completing the entire study protocol.

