**Fig. 3 Fig3:**
[figure not shown]
Protocol for exercise intervention, Reps, Repetitions; nRM, Nonrepetition Maximum; RM, Repetition Maximum

Control groups will be provided with exercise brochures and encouraged to perform home exercise daily. The exercise brochures (Supplemental Material 2) will include stretching, balance training, back extensor strengthening, and other strengthening exercises. Performing home exercise at least twice per day will be instructed and encouraged.

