### Nutritional supplementation

Basal nutritional surveys using 24-hour recall methods will be performed in both groups (exercise and control groups) by a trained dietician. Total calorie and protein intake will be assessed, and the Mini Nutritional Assessment-Short Form at T0 (0 weeks)—with the score ranging from 0–14 points—will be evaluated to assess the nutritional status of participants [22].

Protein supplementation during resistance exercises is known as significantly increasing the muscle size and strength in healthy adults [23]. In our study, two packs of protein complex powder (Selex core-protein; protein: 20 g [50% casein + 40% whey + 10% soy, total leucine: 3000 mg], vitamin D: 800 IU [20 µg], calcium: 300 mg, fat: 1.1 g, carbohydrate: 2.5 g; Maeil Dairies Co., Ltd., Seoul, South Korea) will be provided in daily basis; therefore, a total of 40 g of protein, 1600 IU of vitamin D, and 600 mg of calcium will be provided for the 24-week program in all participants, regardless of allocated group.

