### Outcome measurement and participants’ timeline

The primary outcomes of this study are changes in the skeletal muscle index (SMI) and BMD of the lumbar spine and total hip between the baseline and end of the intervention. The SMI is an indicator of skeletal muscle mass, which is calculated as the appendicular skeletal muscle mass divided by height squared (kg/m^2^). The secondary outcomes are quality of life measurement, functional assessment, bone turnover marker (C-telopeptide [type 1 collagen], CTX), BIA assessment (including body composition and whole-body phase angle), and muscle quality index (MQI). Participants will be screened for adverse events from study inclusion, to the end of the intervention. The schedule of the trial is illustrated in Fig. 4. After obtaining informed consent, basal measurements including demographic details (sex, age, height, weight, alcohol consumption, smoking history, and other medical history) will be surveyed by the research delegate. Weight (kg) divided by the height squared (cm^2^) will be used to compute the body mass index (BMI). Blood samples in fasting status will be collected from the antecubital veins of participants, and analyzed within 24 h of sampling. Albumin, pre-albumin, calcium, parathyroid hormone, serum vitamin D, creatinine levels will be evaluated at T0 (0 weeks).

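### The protocol promises adverse-event screening of participants but rules out asking controls, so control-arm harms can go unrecorded and the reported counts would not be comparable between arms

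*Protocol article*

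**What the plan says.** Two sections of the protocol article set the rule for collecting adverse events.

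- **Outcome measurement and participants' timeline:** "Participants will be screened for adverse events from study inclusion, to the end of the intervention". No arm is excepted.
- **Predicted adverse events and monitoring:** "The potential adverse events that could occur in the exercise group during the intervention will be observed by therapists", and then "participants in the control group will not be queried regarding adverse events". The same section ends with a reporting promise: "The number and seriousness of the adverse events will be reported".

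Three other places bear on whether controls have anything to report.

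- **Nutritional supplementation:** the protein, vitamin D and calcium product "will be provided for the 24-week program in all participants, regardless of allocated group".
- **Exercise protocol (text after Fig. 3):** "Control groups will be provided with exercise brochures and encouraged to perform home exercise daily". It adds: "Performing home exercise at least twice per day will be instructed and encouraged". The brochure covers stretching, balance and strengthening work.
- **Exit criteria:** one ground for leaving the study is "serious side effects preventing further participation", not limited to one arm.

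**The concern.** The sentence about controls is an explicit rule, not a detail that an article leaves to a fuller protocol. It conflicts with the general screening statement, and site staff can follow only one of the two.

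If the monitoring section is followed, two things are at stake. First, controls are not untreated. They are women aged 65 to 90 with low bone density and sarcopenia, they take a daily supplement, and they are encouraged to exercise at home with no supervision described. Falls, joint pain or intolerance of the supplement among them may never be recorded. Second, the article promises to report the number and seriousness of events. Fatigue, arthralgia and falls, which the monitoring section names, also occur without training. A count from an arm under observation, set beside a count from an arm that was not asked, does not show what training added.

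**Working it through.** **1. The two rules side by side**

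| | Timeline section | Monitoring section |
|---|---|---|
| Exercise arm | screened, inclusion to end of intervention | observed by therapists |
| Control arm | screened, inclusion to end of intervention | not asked |

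The control row is contradictory. The monitoring section gives no other route for collecting events in controls.

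**2. How many participants are affected**

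The sample size section plans at least 17 per group and allocation is 1:1, so 17 of 34 participants (half) fall under the sentence. Nothing below depends on how the 17 was derived.

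**3. Contact by arm**

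- Exercise arm: 2 gym visits per week × 24 weeks = up to 48 supervised sessions.
- Control arm: no training sessions, but not zero contact. DXA and CTX are scheduled at weeks 0, 12 and 24, and BIA four times at six-week intervals, with no restriction by arm in the text. These visits are not said to include adverse-event questions.

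**4. What unequal collection does to a comparison**

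The plan states no adverse-event rate, so there is no figure of its own to reproduce. The following is an illustration; the risks and capture fractions are assumptions. Let *p* be the true risk of at least one event, equal in both arms, *e* the fraction captured under exercise and *c* the fraction captured in controls.

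Apparent risk difference = *pe* − *pc* = *p*(*e* − *c*), while the true difference is 0. With *e* = 1:

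| *p* | *c* = 0 | *c* = 0.25 | *c* = 0.5 | *c* = 1 | Chance that at least one of 17 controls truly has an event, 1 − (1 − *p*)^17 |
|---|---|---|---|---|---|
| 0.10 | 0.10 | 0.075 | 0.05 | 0 | 83% |
| 0.20 | 0.20 | 0.15 | 0.10 | 0 | 98% |
| 0.30 | 0.30 | 0.225 | 0.15 | 0 | 99.8% |

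The column *c* = 0 is the extreme, with no spontaneous report at all. If therapists also miss events, *e* is below 1 and the distortion shrinks, but it still runs against exercise as long as *e* exceeds *c*.

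At *p* = 0.30 the expected number in the exercise arm is 17 × 0.30 = 5.1. A recorded split of 5/17 against 0/17 gives a two-sided Fisher p of 0.044; 4/17 against 0/17 gives 0.103. At the extreme, a difference in collection alone could pass for a harm of training.

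**5. What is unaffected**

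The sample size rests on change in skeletal muscle index. Neither it nor the primary outcomes depend on adverse-event collection.

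**The case against.** The strongest reply is that the article plans no safety comparison. Adverse events are neither a primary nor a secondary outcome, and the statistical analysis section gives no test for them. This stands: the distortion arises only if someone compares the reported counts.

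A reader might go further and infer that the recorded control rate will fall to almost nothing, that no valid difference could be computed for any event, or that training is bound to look harmful. The documents do not support this. Controls come to shared assessments and may mention events. A serious event that ends participation could surface through the exit criteria. No capture rate is given. The direction is a tendency, not a certainty.

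Three further points have weight.

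- **Precision.** With 17 per arm even perfect collection is weak. Zero events in 17 leaves a 95% upper limit of 1 − 0.05^(1/17) = 16% one-sided, or 1 − 0.025^(1/17) = 20% two-sided. This limits what the comparison could have shown, but does not justify collecting it unequally.
- **Supplement events.** The monitoring section lists only fatigue, joint pain, exercise injury and falls, and does not say that exercise participants are systematically asked. Supplement-related harms may be missed in both arms.
- **Low expected risk.** The article records that the review board and investigator judged risk to be minimal, and prior fragility fracture and reduced kidney function are exclusions. This lowers the concern without removing it.

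None of these points reconciles the two statements.

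**Conclusion.** The contradiction is real and needs correcting. Under the monitoring section as written, harms in up to 17 of 34 participants can go unrecorded, although those participants receive the supplement and a home-exercise instruction. Any comparison of the reported counts between arms would tend to be distorted against exercise.

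The direction rests on one assumption: that a larger share of events is captured among participants seen by therapists up to twice a week than among participants who are not asked. The size cannot be fixed from the documents. The range of 0.05 to 0.30 in apparent risk difference holds for an assumed equal risk of 0.10 to 0.30, full capture under exercise, and capture of half or none in controls.

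The point concerns participant safety and the reading of the adverse-event counts; the efficacy analysis stands apart from it.

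**What to change.** 1. Reconcile the two sections by deleting the statement that controls will not be asked.
2. Put the same structured adverse-event questions to both arms at the same existing assessment times. Cover falls, fractures, musculoskeletal pain, and gastrointestinal and other supplement-related events.
3. Protect the blinding. One blinded physical therapist performs every assessment, and answers about pain or injury could reveal gym attendance. Use a self-completed form that this assessor does not see, or have the study coordinator, who handles the allocation, ask the questions.
4. Base any comparison between arms on the events collected in this way. List events seen only by therapists at training sessions separately.
5. Allow for the trial being under way: recruitment was due to finish in November 2023 and completion was estimated for December 2024. For follow-up already completed without these questions, state in the report that adverse-event counts are not comparable between arms.

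The cost is a short form, a few minutes per visit and a short amendment. Unasked follow-up cannot be recovered by analysis, so step 5 is needed for anyone who finishes before the change.
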